#### Attrition management

We provide a US$25 incentive to the parents of all participating infants when the infant begins oral feeding and at hospital discharge. We also provide US$25 for each post-discharge visit at 2 and 6 months corrected age. To further enhance retention, we maintain contact with families via Email and postcards to keep up-to-date on addresses and telephone numbers and changing circumstances related to infant health. We send follow-up reminders immediately after discharge to promote higher subject retention and we offer flexible scheduling for the post-discharge visits.

### Intervention

The study intervention has two phases using a tactile experience designed to pattern the neurologic system’s theoretical expectation for feeding experience. Phase 1, a period of “attended gavage,” begins within 24 hours of the first gavage feeding, which is generally provided before 72 hours of life. Attended gavage includes tactile containment during the entire gavage infusion by gravity plus 5 minutes. For infants too ill to be removed from the incubator, tactile containment consists of gentle hand containment (placing one hand lightly over the shoulder area and one hand lightly over the lower extremities). If medically stable, the infant is swaddled and removed from the incubator and held. Infants are also offered nonnutritive sucking (NNS) as part of every attended gavage feeding based on prior research showing that NNS facilitates behavioral organization. Instructions related to the tactile containment, swaddling/holding during gavage, and use of NNS are provided for all nursing staff and parents of infants in the intervention group. Gavage feedings are most often provided on a schedule of every 3 hours. Infants on continuous feedings, which may be needed for some infants primarily because of gastric reflux, receive the attended protocol every 3 hours for 15 minutes. Phase 1 of the intervention has varying duration, lasting as long as 12 weeks for infants born at 23 weeks PMA. Attended gavage is a change in practice for most NICUs so we use a team of well-trained study nurses who provide the attended gavage feedings for a minimum of 50 % of the feedings daily. Nursing staff or parents may provide additional attended gavage feedings. We record the occurrence of each attended feeding including who provided the intervention (parent, nursing staff member, or study nurse) and include that “dose” as a covariate in our analyses.

Phase 2 begins when infants in the intervention group begin oral feedings. When an oral feeding is attempted, the infant is held outside the incubator in a swaddled, flexed position either upright or side-lying. We record the volume of feeding prescribed and the amount consumed at each feeding. Infants who are unable to complete the prescribed volume orally or unable to orally feed receive attended gavage as described in Phase 1.

In both Phase 1 and Phase 2, parents of infants in the intervention group are encouraged to participate by holding their infants for feedings. Feeding at the breast is encouraged for all infants whose mothers have planned to breast feed and the use of breast milk is encouraged for all feedings. Intervention fidelity is monitored on a quarterly basis to ensure that infants in the intervention group receive a minimum intervention dose of 50 %.

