### Usual care

Infants in the usual care group do not receive the tactile intervention during gavage feedings, including those that occur when the infant is in the transition period from gavage to oral feeding. When infants receiving usual care are gavage fed, they are almost always in the incubator and they are not handled or touched during the feeding. While the infant may be in a “nested” position using positioning devices, nurses rarely swaddle infants, use their hands to contain infant movements, or hold infants during gavage feedings. Occasionally these infants are swaddled and held by their parents during gavage feedings. However, this occurs only rarely and without any consistency. We are recording all occurrences of any tactile exposure usual care, control group infants receive during gavage feedings.

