The secondary aims require similar comparisons between study groups on secondary outcomes (cognitive functioning, neurobehavioral development, and clinical outcomes). To test secondary aim 1, differences between the 2 groups on the cognitive outcome measure (BSIDIII cognitive subtest scaled score) at 6 months corrected age will be tested using an ANCOVA with morbidity (NMI) and birth gestation used as covariates. To test secondary aim 2, 4 analyses will be performed, one for each of the feeding-related neurobehavioral outcomes (sucking organization, 2 measures of feeding performance, and HRV). The modeling will be done as above with a repeated-measures mixed-model approach with covariates (birth gestation, morbidity). To test secondary aim 3, separate ANCOVA analyses of the clinical outcomes (time to full oral feeding and length of stay) will be used to compare the 2 groups with the birth gestation age and morbidity covariates.

The intent of the exploratory aim is to identify risk factors of poor neurobehavioral development and cognitive dysfunction in preterm infants. We will test the assumed comparability of randomly assigned groups prior to undertaking further analyses. Secondary analyses will focus on the interactions between risk factors and the intervention differences by first screening the risk factors for effects at *P* = 0.2 and then developing a single exploratory model that includes all of the risk factors that significantly influence the outcome differences between the groups. Additional analyses will focus on the findings for neurobehavioral development including sucking organization and feeding performance, HRV, and clinical outcomes, first by examining the relationships between the risk factors and the components of neurobehavioral development and then by assessing the relationships among the components of neurobehavioral development and the primary outcome measure, the NAPI score (neurobehavioral outcome). The final goal is to identify a model of risk factors, modifiers (measures of neurobehavioral development), and mediators (intervention) that have an effect on the differences between groups.

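### The protocol makes delivered feeding dose, a post-randomisation variable that nearly separates the arms, a covariate without saying in which models, and nothing keeps it out of the primary ANCOVA

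*Protocol article*

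**What the plan says.** Three parts of the protocol article bear on this.

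- **Intervention.** Attended gavage is logged feed by feed: "We record the occurrence of each attended feeding including who provided the intervention (parent, nursing staff member, or study nurse". The plan for using that log in the statistical models is brief: "and include that “dose” as a covariate in our analyses". The sentence does not say which analyses. The same section sets a fidelity check each quarter "to ensure that infants in the intervention group receive a minimum intervention dose of 50" per cent.
- **Usual care.** "Infants in the usual care group do not receive the tactile intervention during gavage feedings". Parents sometimes swaddle and hold control infants during gavage: "However, this occurs only rarely and without any consistency". Control exposure is logged too: "We are recording all occurrences of any tactile exposure usual care, control group infants receive during gavage feedings". A dose value can therefore be formed in both arms.
- **Data management and analysis.** The primary comparison on the NAPI is a repeated-measures ANCOVA in a mixed model, with no covariates named. Secondary aim 1 uses "an ANCOVA with morbidity (NMI) and birth gestation used as covariates". Secondary aims 2 and 3 name the same two covariates. Dose is not mentioned anywhere in this section.

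**The concern.** Delivered dose is a consequence of allocation and a large part of what is allocated. With dose in the model, the group coefficient compares PFE and usual-care infants who received the same dose. The design is meant to leave almost no such infants, so the contrast is an extrapolation. It is also a different quantity from the effect of being assigned to PFE, which is what the primary and secondary aims ask about.

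There are two consequences. Collinearity between arm and dose inflates the standard error of the group term. In addition, whatever part of the benefit runs through the amount of attended feeding is credited to the dose coefficient and taken away from the group term. An effective intervention could then be reported as ineffective. Because the primary model has no covariate list, the Intervention sentence is the only text naming a covariate that could apply to it.

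**Working it through.** **Inputs from the protocol.** 120 infants, 60 per group (Sample); 20 % attrition, 0.7 SD, two-sided 0.05 and at least 90 % power by a two-group t-test (Power analysis); a dose minimum of 50 % in PFE (Intervention); rare exposure in usual care (Usual care).

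**Inputs assumed.** The documents give no dose distribution. Three pairs of uniform ranges are used. One lets PFE fall to 40 %, because the 50 % is a monitored target.

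**Step 1: the plan's own figure, without dose.** 120 × 0.8 = 96, or 48 per arm. The standard error of the group difference is √(2/48) = 0.204 SD. The noncentrality is 0.7/0.204 = 3.43, and noncentral-t power is 92.4 %. This agrees with the stated figure of at least 90 %.

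**Step 2: dose added as a share of feeds, effect belonging to the arm.** With equal arms, mean dose difference m and average within-arm dose variance v (width²/12 for a uniform range), the variance inflation for the group term is VIF = 1 + m²/(4v). The standard error becomes 0.204 × √VIF and the noncentrality 3.43/√VIF.

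| Assumed dose, PFE / control | m | v | VIF | SE (SD) | Noncentrality | Power |
|---|---|---|---|---|---|---|
| 50–100 % / 0–10 % | 0.700 | 0.01083 | 12.3 | 0.72 | 0.98 | 16 % |
| 50–80 % / 0–5 % | 0.625 | 0.00385 | 26.3 | 1.05 | 0.67 | 10 % |
| 40–100 % / 0–20 % | 0.600 | 0.01667 | 6.4 | 0.52 | 1.36 | 27 % |

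For the first row, v = (0.5²/12 + 0.1²/12)/2 = 0.01083 and VIF = 1 + 0.49/0.0433 = 12.3. A simulation with 3,000 replicates per scenario agrees: VIF 12.6, 27 and 6.5, and power 16 %, 11 % and 27 %.

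**Step 3: dose added as a share, effect proportional to that share.** Dose then explains the whole effect, so the group coefficient has expectation zero. Simulated means were 0.02, −0.03 and −0.01 SD, with rejection in 4–5 % of trials. The same data analysed without dose gave about 0.70 SD and about 92 % power.

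**Step 4: dose as a count of attended feeds.** Assumptions: gavage for 1–2 up to 12 weeks, 8 feeds a day (24 h / 3 h), 50–100 % against 0–10 % attended, and gavage duration also in the model. Counts vary more within the PFE arm, so VIF is about 4–5. Noncentrality is 3.43/√4 = 1.71 to 3.43/√5 = 1.53, which gives power of about 40 % to 33 % when the effect belongs to the arm. Simulations varying these assumptions gave about 32–44 %.

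**Step 5: dose also related to prognosis.** Suppose healthier infants receive more attended feeds, with an assumed correlation of about 0.5 between an underlying prognostic factor and dose. The adjusted group coefficient averaged −1.03 to −2.00 SD when the effect ran through dose, and −0.31 to −1.31 SD when it did not. The unadjusted estimate stayed at about 0.70 SD.

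These checks use a single outcome time, as in the plan's t-test calculation, with one dose value per infant.

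**The case against.** The strongest reply concerns scope. The dose sentence stands in the description of the intervention and refers only to analyses in general. Where models are specified, dose is absent, and all three secondary aims have covariate lists without it. This stands. A reader might infer that dose enters every model that tests an aim. The documents do not show that, and for the secondary aims the specific lists point the other way. The reply does not clear the primary model, which has no list and no exclusion.

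Other limits also stand:

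- **Nature of dose.** The article does not define dose as a share; it could be a count. On the count reading the loss of power is smaller, though still serious.
- **Dose is not all of PFE.** Oral feeding in a swaddled, flexed position and encouragement of parental holding are also part of it. A reader might infer from the theory that benefit is proportional to dose. No section says so, so the zero coefficient is a limiting case.
- **Intent-to-treat.** A reader might see a direct contradiction with the promised intent-to-treat analysis. That sentence describes the dataset, all infants as opposed to completers. Dose adjustment would defeat its purpose but does not contradict its words.
- **Morbidity index.** A reader might extend the point to the NMI, because no scoring cut-off is given. That is detail which an article commonly leaves to a fuller document, and it is no part of this finding.

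**Conclusion.** The point holds as an unrestricted rule that the plan does not reconcile. The Intervention section makes dose a covariate, the primary ANCOVA does not exclude it, and the secondary-aim lists omit it. In any between-group model that does include dose, the group term is not the randomised effect of PFE.

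The direction does not depend on the assumed numbers, because dose follows allocation and the design pushes the arms apart on it. The size does depend on them. From about 92 %, power falls to about 10–27 % (share) or about 32–44 % (count, duration in the model) when the effect belongs to the arm. When the effect is proportional to the share of feeds attended and that share is the covariate, the group coefficient is about zero with about 5 % rejection. Since the affected model may be the primary one, this should be settled before analysis.

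**What to change.** 1. State in the analysis section that delivered dose is excluded from all between-group models testing the primary and secondary aims, and that these use randomised arm and baseline covariates only.
2. Replace the dose sentence in the Intervention section with one that confines dose to a separate dose-response or adherence analysis, labelled exploratory and observational, and say whether dose is a share or a count.
3. Reconcile the Intervention section with the primary and secondary model descriptions, and list the primary model's covariates.

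An instrumental-variable or complier analysis is optional and is not needed to resolve the point. The cost is wording only: no new data and no change to sample size or conduct. The article gives the trial status as recruiting, so the change can be made before analysis.

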### Usual care

Infants in the usual care group do not receive the tactile intervention during gavage feedings, including those that occur when the infant is in the transition period from gavage to oral feeding. When infants receiving usual care are gavage fed, they are almost always in the incubator and they are not handled or touched during the feeding. While the infant may be in a “nested” position using positioning devices, nurses rarely swaddle infants, use their hands to contain infant movements, or hold infants during gavage feedings. Occasionally these infants are swaddled and held by their parents during gavage feedings. However, this occurs only rarely and without any consistency. We are recording all occurrences of any tactile exposure usual care, control group infants receive during gavage feedings.

### Measures

Neurobehavioral organization will be measured using the Neurobehavioral Assessment of the Preterm Infant (NAPI) [22]. Cognitive function will be measured using the Bayley Scales of Infant and Toddler Development, Third Edition, (BSID III) [23]. Neurobehavioral development will be measured using sucking organization, feeding performance, and heart rate variability. Clinical outcomes are measured using data obtained from the health record. Data for risk factors associated with neurodevelopmental outcomes are obtained from the health record or from biologic samples obtained specifically for the study.

#### Neurobehavioral organization

The NAPI is used to measure neurobehavioral organization. The NAPI measures seven domains of neurobehavior and assesses the effect of NICU interventions. It is a non-intrusive, objective assessment of the infant’s maturity of functioning with construct validity with neonatal morbidity. We will use mean scores for each domain in our analyses with particular attention to the alertness and orientation score. The NAPI can be administered with the infant in an incubator or open crib and can be used if the infant is receiving oxygen; some items are not used if the infant is on mechanical ventilation. The assessment is done at least 30 minutes before feeding and uses a standardized format maximizing the opportunity to test various functions in appropriate behavior states. Most of the exam is observational and does not require handling the infant. The NAPI is administered at baseline, transition to oral feeding and NICU discharge assessments at the infant’s bedside by an experienced NAPI examiner. The NAPI assessment at 2 months corrected age is completed by the same examiners at the follow-up clinic. The NAPI is predictive of early developmental delay and later motor development, neurobehavior, and cognition; NAPI scores on alertness and orientation skills at 36 weeks PMA predict BSID III outcomes.

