#### Power analysis

The proposed sample size for the study is based on associations between measures of feeding experience and components of neurobehavioral development and neurobehavioral organization discovered in our previous studies [18–21]. We anticipate 20 % attrition, primarily for medical conditions that arise or are diagnosed after enrollment. The sample size was determined by assuming each aim will be tested using 2-sided tests at *P* = 0.05. For the primary aim, we expect to detect an effect size of at least 0.7 standard deviation (SD) between groups on the final neurobehavioral score, with at least 90 % power using a 2-group *t*-test. However, a random effects model that takes into account the repeated measurements over time is proposed for the analyses of neurobehavior. Differences of the same effect size should improve the power to at least 95 % because of the additional number of observations. Although we have powered the study to test the primary aim, we also considered power for the additional aims. For secondary aim 1 involving a test of the effect of the intervention on cognitive function at 6 months, the same sample size analysis indicates a 2-unit difference (SD = 3) on cognitive development will be detected with 89 % power with only a 2-group *t*-test; the analysis of covariance (ANCOVA) should have more power. For secondary aim 2, the analyses and the sample size calculations are the same as with the primary aim. Secondary aim 3 will be tested in a manner similar to secondary aim 1 and so the sample size calculations should be similar. For the exploratory aim a sample of 96 infants in a test for zero correlation will provide at least 90 % power to detect *r* ≥ 0.26 and at least 80 % power to detect *r* ≥ 0.21.

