Heart rate variability (HRV) is a measure of ANS maturation and an indication of infant well-being and development [35, 36]. HRV increases with increasing PMA and, as the infant is more able to control breathing, an increase in parasympathetic activity occurs, as seen in the high frequency (HF) power spectrum of HRV. Both parasympathetic and sympathetic activity is seen in the low frequency (LF) power spectrum. Higher respiratory rates and activity result in a higher LF:HF ratio, consistent with a stress model. HRV effects have been found to be associated with poor autonomic organization during feedings. We examine HRV twice a week during observation feedings with data collected by the acquisition system described above. The electrocardiogram waveform is sampled at a rate of 1000 samples/second; the instantaneous R-R time interval is used for computation of HRV after being digitally filtered to remove artifact. HRV includes the LF and HF proportions (in normalized units) and the LF:HF ratio.

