### Data management and analysis

A relational database has been created. Monthly assessment of data entry processes and a quarterly audit of random samples for completeness are conducted. During the electronic data acquisition process, all sampled data from each of the physiologic channels are stored in a single file. To prepare these data for analysis, the data are digitally filtered to remove frequencies not part of the physiologic signal spectrum. The filtered signal is then applied to our algorithms resulting in the relevant parameters.

Descriptive statistics will be computed for all demographic data to describe the sample and check for missing and outlying data. Descriptive statistics will also be computed for all component measures of study variables. Transformations of non-normally distributed variables will be used for analyses as indicated. Because measures are repeated on the same infant, all analyses will take into account the dependency between measures. Because some infants may be unable to complete the study due to unexpected illness, there will be an “all-infants” dataset (all eligible) and a “per-protocol” dataset (all completers). An intent-to-treat analysis will be performed on the all-infants dataset using all measures obtained. An analysis on the “per-protocol” dataset will be performed using the data from the infants who completed the entire study. All results will be reported as described by the CONSORT guidelines [17]. Analyses will be performed using SAS (SAS Institute Inc., Cary, NC, USA) at an overall alpha = 0.05 significance level.

The primary aim states that infants who receive the PFE will have improved neurobehavioral organization at transition to oral feedings, NICU discharge, and 2 months corrected age (48 weeks PMA). The difference between the PFE and usual care groups on the NAPI will be tested using a repeated-measures ANCOVA. A mixed-model will account for the correlation between the measurements at each time point and allow for differential patterns of missing values at the three time points. A significant difference across these time points will be followed by separate comparisons at each time point; each will be performed at the *P* = 0.05 level of significance.

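### The primary NAPI outcome is not uniquely fixed: seven domain scores are to be analysed, but the power and the overall 0.05 fit only one

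*Protocol article*

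**What the plan says.** - **Neurobehavioral organization.** "The NAPI measures seven domains of neurobehavior and assesses the effect of NICU interventions". On what is analysed: "We will use mean scores for each domain in our analyses with particular attention to the alertness and orientation score". The alertness and orientation score is also said there, as measured at 36 weeks PMA, to predict BSID III results.
- **Power analysis.** Each aim is assumed to be tested two-sided at 0.05. The target for the main comparison reads: "we expect to detect an effect size of at least 0.7 standard deviation (SD) between groups on the final neurobehavioral score". The power stated for this, by a two-group t-test, is 90% or more. Attrition of 20% is expected.
- **Data management and analysis.** The groups are compared on the NAPI, with no domain named, by a repeated-measures ANCOVA fitted as a mixed model over three time points. "A significant difference across these time points will be followed by separate comparisons at each time point", each at the 0.05 level. All analyses are run "at an overall alpha = 0.05 significance level". Later in the section the primary outcome measure is called the NAPI score, in the singular.

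The article defines no NAPI composite and sets no order or adjustment across domains.

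**The concern.** Three statements do not fit together: the mean scores of all seven domains enter the analyses, the trial is powered on one score, and the overall error rate is 0.05. They can be reconciled only if one domain is primary, a composite is defined, or the error rate is shared among the domains. The article does none of these.

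The error rate attached to the trial's main claim is therefore unknown. The score that carries the primary conclusion could also be settled after the results are seen. A favourable result on one domain out of seven would have no agreed standing, because nothing fixed in advance says whether it meets the primary aim.

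**Working it through.** **Inputs from the article.** 120 infants, 60 per group (Sample). Attrition 20%, effect 0.7 SD, two-sided 0.05 (Power analysis). Seven domains (Neurobehavioral organization). Three time points (Data management and analysis).

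**Assumption.** The article gives no correlation between domains or between time points, so a range is shown.

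**1. The plan's own power figure.** Evaluable infants per group: 60 × 0.80 = 48. Noncentrality: 0.7 × √(48/2) = 3.43. With 94 degrees of freedom the two-sided 0.05 critical value is 1.986. The noncentral t distribution gives power 92.4% (92.9% by the normal approximation). This agrees with the stated 90% or more, and it is the power of one test of one score at an undivided 0.05.

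**2. Error rate over seven domains, if each is tested at 0.05.** With independent domains: 1 − 0.95⁷ = 0.302. With a common correlation ρ between the seven test statistics (two-sided normal tests):

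| Assumed ρ | Chance of at least one false-positive domain |
|---|---|
| 0 | 30% |
| 0.3 | 27% |
| 0.5 | 23% |
| 0.7 | 18% |
| 0.9 | 11% |

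Even at 0.9 the rate is about twice the claimed 5%.

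**3. Power if the overall 0.05 were instead kept by an equal split (illustration only).** 0.05/7 = 0.00714. With 48 per group the critical value is 2.750, and power for 0.7 SD on any one domain is 75.0% (t) or 77.0% (normal). Keeping 90% would need 67 (t) or 65 (normal) evaluable infants per group. That is 67/0.80 = 83.75, so 84, or 65/0.80 = 81.25, so 82 enrolled per group: 164 to 168 in total against the planned 120.

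**4. Time points within one score.** The overall test controls error when no time point differs. If one time point truly differs and the overall test is passed, the other two are each tested at 0.05. The chance of at least one false positive among those two is 1 − 0.95² = 9.75% if independent, 8.3% at a correlation of 0.7 and 7.0% at 0.9, so about 7% to 10%.

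**The case against.** The strongest reply is that no sentence sets 0.05 for each domain. The per-comparison 0.05 in Data management and analysis refers to the time points, Power analysis sets 0.05 for each aim, and the primary test is described as one test of the NAPI. This stands. The 11% to 30% is conditional on a per-domain level that is implied only because no other level is given.

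Several stronger readings are tempting, and the article does not support them:

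- *The primary aim is met if any one of the seven domains is significant.* No such success rule is written. The article leaves the rule open.
- *The power calculation is wrong.* It is correct for one score. The 75% arises only under a seven-way Bonferroni split, which the article does not propose.
- *The time-point comparisons are unprotected.* They follow a significant overall test. The 7% to 10% arises only when one time point truly differs, so the conclusion that the intervention affects the NAPI score is then true and only its timing may be misstated.
- *Secondary aim 2 has the same fault on the same scale.* It has four planned analyses and more component variables than that. But a false-positive rate that counts those components as independent cannot be justified, since the HRV measures are closely related. Choosing one variable per construct may properly be left to the analysis plan.

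Two further replies carry less weight. One is that alertness and orientation is in effect primary. Particular attention is emphasis, though: the same sentence commits every domain to the analyses, and neither the power section nor the analysis section names that score. The other is that a separate analysis plan may settle multiplicity. It may, but the problem here is not an absent detail. The article's own statements about what the primary outcome is, and what its error rate is, conflict.

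**Conclusion.** The point holds as an inconsistency in the definition of the primary outcome. Seven domain scores are to be analysed, one score is powered, and an overall alpha of 0.05 is claimed with nothing to connect them.

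If the domains are each tested at 0.05, the family-wise error is about 30% under independence, 23% at a correlation of 0.5, 18% at 0.7 and 11% at 0.9. These figures rest on the implied per-domain level and on assumed correlations. The stated power of at least 90% (92.4% at 48 per group) holds only if there is a single primary score. The time-point issue is real but minor.

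**What to change.** - **Primary score.** Name one primary NAPI score in both the outcome and the analysis sections. Alertness and orientation is the candidate the article already singles out. Test it over the three stated time points with the planned mixed model at two-sided 0.05. The overall 0.05 then holds for the primary aim, and the power statement stands with 120 infants.
- **Other domains.** Make the remaining six secondary, with a Holm adjustment among them.
- **Time points (minor refinement).** Apply Holm to the three comparisons that follow a significant overall test. Keep all three time points in the primary aim: making one of them the sole primary contrast would change the aim as stated in Background.

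The cost is wording. Trial status says recruitment is still open, so the change can be made and dated before group results are seen. The downside is that claims on the other six domains, and on single time points, will need stronger evidence.
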